**n. Statistical statement:**

The design of the drug trial is exploratory in nature. Though a randomized selection of patients will be done to either of the two arms, the sample size is that of convenience (expert opinion) and the same is not statistically powered however, sample size (70 patients in each arm) sufficient to draw meaningful conclusions. The statistical significance p<0.05(two sided) is predefined for analysis. Statistical analysis will be performed using standard tests to compare the two interventional arms for primary and secondary efficacy measures. Safety events will be also analyzed. Both intent-to-treat and per protocol completer analysis will be performed. Regression analysis will be done to identify predictors of response.

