# 11. EFFECTIVENSS MEASURES

**11.1 Primary Efficacy:**

1. Mean time (days) for clinical recovery (Day of randomization to the Day of clinical recovery (see criteria below] [Time Frame: up to 28 days]
2. Proportion of patients showing ‘clinical recovery’

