**17.1 Sample Size:**

A convenience sample size of 70 patients in each of the arm is selected. The total sample size will be 140 patients in each of the 3 studies. The sample size is not based on any power calculations but by consensus within the experts of the Working Group constituted for the purpose of this protocol. It is assumed that the withdrawal rate may be in the range of 15-20%.

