**17.2 Statistical Analysis:**

Whenever suitable, both completer and an intent-to-treat analysis with ‘last observation carried forward’ will be performed; for intent-to-treat analysis the patient should have completed at least 4 weeks of intervention and completed the follow up visit at 4 weeks post enrollment.

All statistical processing will be performed using SPSS & BMDP software unless otherwise stated.

The data will be individually analyzed for central tendencies (mean, median), range, standard error, standard deviation and 95% confidence intervals for each intervention arm in each of the groups in the study. Data will be tabulated and graphically shown using standard format and MS Excel and other software programs. Though ANOVA will be used for most of the measures, standard parametric (Student t-test) and non-parametric statistical tests (Mann Whitney statistic, Kruskal Wallis test) will be used depending upon the normality of the data. Fisher’s exact test or Chi Square will be used to test the proportion of patients classified as efficacy failures and those with AE (calculate exact binomial 95% Confidence Interval).

The primary efficacy measures of ‘mean time to clinical recovery’ and ‘proportion of patients with clinical recovery’ in the two arms will be compared using appropriate statistical tests; ANOVA for ‘mean time’ and two proportion z-test for proportion of patients.

Secondary efficacy measures in the two arms will also be compared and Bonferroni correction will be applied for multiple comparisons.

Risk ascertainment will be done for selected variables. Regression analysis (multivariate and step down) will be used to identify predictors for important outcomes. Survival analysis will be carried out to compare the two interventions (HCQ and Ashwagandha) for primary efficacy at different study time points.

Within arm efficacy will be evaluated by a one sample Student t-test.

Significance for each statistical test result will be considered at two-sided p< 0.05.

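### Two primary outcomes are each tested at two-sided 0.05 with no order, alpha split or success rule; if either alone may be claimed, the chance of a false positive is about 7-10%

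*Combined protocol and SAP*

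**What the plan says.** Section 11.1 (Primary Efficacy) lists two outcomes under one heading. The first is "Mean time (days) for clinical recovery (Day of randomization to the Day of clinical recovery", with a time frame of up to 28 days. The second begins "Proportion of patients showing" and refers to clinical recovery; no day is attached to it. The synopsis (item j) lists the same pair.

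Section 17.2 assigns a separate test to each: ANOVA for mean time "and two proportion z-test for proportion of patients". The section closes with "Significance for each statistical test result will be considered at two-sided p< 0.05". The synopsis (item n) adds "The statistical significance p<0.05(two sided) is predefined for analysis".

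The only multiplicity provision is in Section 17.2: "Secondary efficacy measures in the two arms will also be compared and Bonferroni correction will be applied for multiple comparisons".

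The document contains no ranking of the two primary outcomes, no division of alpha, no test order and no rule on whether one or both must be significant. The trial is called exploratory in its title, in synopsis items f and n and in Section 17. On size, Section 17.1 says "A convenience sample size of 70 patients in each of the arm is selected" and disclaims any power calculation.

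**The concern.** The plan recognises multiplicity but corrects for it only among the secondary measures. For the primary outcomes, which carry the trial's main message, the report writer is left to decide after the fact what a positive result is. If time is significant and the proportion is not, or the reverse, nothing in the plan prevents either from being presented as primary success. A reader who sees p<0.05 on a primary outcome will usually take 5% as the chance that the primary conclusion is a false positive. With two unranked opportunities that chance is higher, by an amount that depends on how strongly the two tests are correlated.

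**Working it through.** **Inputs from the documents**
- Alpha 0.05, two-sided, for each test (Section 17.2; synopsis item n).
- Two primary outcomes (Section 11.1), tested by ANOVA and by a two-proportion z-test (Section 17.2).
- 70 patients per arm; withdrawal 15-20% (Section 17.1). At 20%, 70 × 0.80 = 56 per arm.
- 28-day frame for time to recovery (Section 11.1).
- Table 2 of the literature review: median time to recovery 10 days, IQR 7-14, in a Chinese hospital cohort of 138.

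**Assumptions, because the documents give no figure**
- The proportion is also read at Day 28.
- The share recovered by Day 28, and the correlation between the two tests, are varied.
- Either outcome alone counts as a positive primary result.

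The plan states no overall error rate for the pair, so there is no figure of its own to reproduce beyond 0.05 per test.

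**Step 1: limits.** Independent tests: 1 − (1 − 0.05)² = 1 − 0.9025 = 0.0975. Upper bound under any dependence, if each test has exact size 0.05: 0.05 + 0.05 = 0.10. Perfectly correlated tests: 0.05.

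**Step 2: dependence.** For bivariate normal statistics with correlation ρ, the error is 1 − P(|Z₁| < 1.96 and |Z₂| < 1.96). Only the absolute value of ρ matters.

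| ρ | 0 | 0.3 | 0.5 | 0.7 | 0.8 | 0.9 |
|---|---|---|---|---|---|---|
| At least one false positive | 0.0975 | 0.0951 | 0.0907 | 0.0835 | 0.0781 | 0.0704 |

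**Step 3: simulating the two planned tests with no drug effect.** Weibull recovery times (shape 1.5), 28-day cut-off, 20,000 runs per setting, 70 or 56 per arm:

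| Assumed recovery by Day 28 | Non-recovered set to Day 28 | Mean over recovered patients only |
|---|---|---|
| 50-95% | 0.078-0.091 (absolute correlation 0.47-0.76) | 0.091-0.102 (correlation about 0) |
| 98% | 0.065-0.069 | 0.066-0.073 |

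At 98% recovery the z-test is conservative: its own error is about 0.025 at 70 per arm and 0.016 at 56, which pulls the total down.

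A log-normal fitted to the Table 2 figures has σ = ln(14/7)/1.349 = 0.514. The share recovered by Day 28 is then Φ(ln(28/10)/0.514) = Φ(2.00) = 0.977. With that distribution alone, the chance of at least one false positive is 7.6% (others set to Day 28) or 8.0% (recovered only) at 70 per arm, and 6.7-7.0% at 56. Adding 10-20% who never recover gives 7.9-8.1% and 9.9-10.0% respectively at 70 per arm. Over all settings with 5-20% added non-recovery the range is about 7.5-10.5%.

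Values slightly above 10% do not contradict the bound. The z-test's own simulated error reached 0.0537 in some settings, so its size is not exactly 0.05. Simulation error adds about √(0.10 × 0.90 / 20,000) = 0.002.

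**Step 4: what a rule would do.**
- Fixed sequence: the second test is reached only if the first is significant. With no effect on either outcome, a false positive therefore requires the first test to err, at 0.05. If the first outcome has a real effect, only the second can err, again at 0.05.
- 0.025 each: 1 − 0.975² = 0.0494 if independent, 0.0465 at ρ = 0.5, 0.0402 at ρ = 0.8.
- Both required at 0.05: 0.05² = 0.0025 if independent, rising to just under 0.05 as ρ nears 1.

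**The case against.** The strongest reply is that the trial is exploratory, unpowered and makes no claim about an overall error rate; strict control across primary outcomes is mainly a confirmatory requirement. This stands as a reason for lower severity. It does not dispose of the point: the same plan names primary outcomes, fixes p<0.05 in advance, applies Bonferroni elsewhere, and in synopsis item n calls the sample large enough for meaningful conclusions.

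A second reply is that the inflation is conditional. A reader might infer that the plan's primary false-positive rate simply is 8-10% instead of 5%. The documents do not support that. They nowhere say that either outcome alone is enough, and the notes to Fig 1 describe primary efficacy as one concept, clinical recovery. If both outcomes were required, the error would be at most 5%. Nor do they give a recovery rate: Section 8 expects the large majority to recover completely, and near 98% recovery the figure is about 7-8%. It would likewise be wrong to infer that the plan promises 5% overall and breaks the promise, since its threshold is stated per test.

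A third reply is that the Bonferroni sentence covers all comparisons. Its subject is the secondary measures, and the section's closing sentence sets 0.05 for each test, so this reading is weak.

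**Conclusion.** The point holds as an unstated success rule with a conditional consequence. If either primary outcome may be claimed alone, the chance of at least one false positive is about 7-10% per drug trial. It is near 7-8% when about 98% recover by Day 28 (lowest single setting 6.5%, at 56 per arm), about 7.5-10.5% when 5-20% do not recover, and 9.75% under independence. The spread comes from the assumed recovery rate and from how non-recovered patients enter the mean, which the plan does not settle.

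The figures exclude the further choices in Section 17.2 between completer and intent-to-treat analyses, and between ANOVA and survival analysis of primary efficacy. Those would add to the chance if any of them could be claimed. Given the exploratory label, this is something that should be fixed, not a defect that invalidates the trial.

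**What to change.** In Sections 11.1 and 17.2, with synopsis items j and n aligned, and before any outcome data are seen:

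1. Test time to clinical recovery up to Day 28 first, at two-sided 0.05. State how patients not recovered by Day 28 stay in the analysis, for example censored at Day 28 with a time-to-event test, or set to Day 28.
2. Define the second outcome as the proportion recovered by Day 28, and test it at two-sided 0.05 only if the first test is significant.

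This holds the error for the pair at 5% without reducing the alpha of the first test. It needs a few sentences and no change to visits, procedures or sample size. The cost is that the proportion can no longer support a positive claim by itself. If the sponsor wants either outcome to stand alone, testing each at 0.025 also keeps the error within 5%, at the price of a stricter threshold for both. Stating that both must succeed is a third option that controls the error, but it makes a positive result harder to reach.

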# 18. MANAGEMENT ISSUES

18.1 **Protocol Violation**:

Any deviation from the protocol is not permitted, except in an emergency situation. The study investigator and the team will be fully conversant with the main provisions of this protocol and exercise utmost care and responsibility while discharging their duty and also ensure utmost compliance by the patients.

If circumstances permit, the investigator attending such an emergency will contact the Chief Principal Investigator at the earliest opportunity so that a decision can be made whether or not to continue the patient in the study.

Any administrative or technical modification, which does not interfere with the patient’s health interests, should be in writing and filed as amendments to the protocol.

The concerned chief investigator will sign these amendments and obtain early clearance from the concerned ‘Ethics Committee’ and the Principal Investigator of the clinical project before finalizing the amendment for execution.

18.2 **Withdrawal of Study Patient:**

Patient may be withdrawn from the study at their own request or at the discretion of the investigator. In all cases, the reasons why the patient is withdrawn will be entered in the CRF. Several likely reasons of withdrawal from study are listed in Section 9 above. As far as possible, a complete final examination must be carried out in all patients who are withdrawn prematurely before the study completion similar to that required on study completion.

18.3 **Safety Issues**: Safety assessments will be based on results of the physical examinations (including vital signs), laboratory tests and adverse events as described above. It is very important that the physician investigators record every adverse event, irrespective of its causality, meticulously in the patient case records. It will also be mandatory and binding for the study physician investigators to keep close contact and co-ordination with the pre-designated principal physician investigators for this purpose and as per instructions from the Sponsor.

Serious adverse events (SAEs) will be tabulated per patient and reported as per GCP guidelines. Each investigation site will submit an updated list of patients who discontinued from the study and a list of patients who experienced SAE to the pre-designated principal investigators of this study as decided by the sponsor.

# 19. ADMINISTERATIVE ISSUES

**19.1 Study Documents**

A Patient Information Sheet (see Appendix H) will be handed over to each patient participant in an easy to understand question answer format and in the language best understood.

Only the patient’s initials / ID number will be used for identification in the study records and database.

Study confidentiality will be maintained. The following documents will be used in the study:

- Patient Case Record Forms (CRF): This will be provided for each study participant. All centers must follow instructions for filling of CRF that have been listed in the beginning of each CRF file.
- Informed Consent in the regional language best understood by the study participant.
- Adverse Event Form
- Serious Adverse Event Form
- Termination Form
- Medication Log
- WHO- Quality of Life

All the centers will be provided with a file in which to organize and retain all study-related documents. All study correspondence should be filed by the investigator in this file. The Site Master File will be available for inspection by the individual monitoring the study in order to ensure that all the relevant documents are present and easily retrievable.

**19.2 Study Participation Cards**

A study pocket sized card (Appendix S) will be provided to each study participant on enrollment and this will be carried on self during the study period. The card will indicate the Patient ID, study medication and contact details of investigator. The patient will be encouraged to show this card to any other medical practitioners while consulting them for any illness.

**19.3. Mobile phone Application**

A special software program as mobile application (AYUSH COV-2 CT App) will be downloaded by the study participant under supervision of the study investigator at the time of enrollment. The App will have a 2-way communication between participant and local investigator-through SMS and phone call. It will also record DAILY the response of the participant to 5 cardinal questions regarding presence and absence of =Fever, Sore throat, Cough, Breathlessness and Suspected Drug Side Effect. In addition, there will be a 6^th^ question- ‘do you wish to speak to investigator’. The participant will complete the response every day between 8-10 pm. The App will send the response daily to the study computer of the local investigator and central monitoring cell (CMC). In case, the study patient fails to complete the response in time, the App will raise a frequent alarm bell pop up response on the mobile phone of the study participant. In case, the response is YES to any of the questions, there will be an alarm bell type visual and audible response raised both the desktop computer and mobile phone of the local investigator and person in charge CMC. This will ensure speedy necessary action by the local site investigator. The App will stay active throughout the study duration.

**19.4 Ethics Committee Approval**: A copy of the formal written notification approving the study will be obtained from the EC duly signed by the chairman or any person so authorized, prior to commencement.

**19.5 Case Record Forms**: All complete CRFs duly signed by the investigator and counter signed by principal investigator must be submitted within one month of the completion of the study to the Principal Investigator.

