**Fig 1: Study Flow Diagram with Schedule of Important Study Events**

Screening of Voluntary and Consenting In-patients suffering from Mild to Moderately Severe COVID-19 for Eligibility as per Inclusion-Exclusion Criteria

3 Ayurveda formulation drug trial studies under a common protocol

(Separate study for each AYUSH 64 / Yashtimadhu / Samshamai Vati Plus)

Randomize Eligible Hospitalized Patients

(Open Label, Parallel Efficacy, Active Control Standard of Care (SOC), Two Arm Study)

Selected Ayurveda Formulation (Adjuvant) Versus SOC (Active Control)

Time Points

Clinical Assessment

Investigations

Baseline

Case Record Form (CRF), Medical History Clinical Examination, Ayurveda Assessment, Health Status (WHOQs), QoL (HR-BHF)

Diagnostic (PCR), Serology (IgM, IgG), Routine Hematology Profile, Special Assays, X-Ray Chest & Imaging, ECG

Week 4

Brief Clin Exam, Ayu Exam, Health Status (WHO- Qs) & QoL (HR-BHF Qs), Adverse Events (AEs)

Diagnostic (PCR), Serology (IgM, IgG), Routine haematology Body Profile, Special Assays

Week 8

Brief Clin Exam, Ayu Exam, Health Status (WHO- Qs) & QoL (HR-BHF Qs), Adverse Events (AEs)

Diagnostic (PCR), Serology (IgM, IgG), Routine haematology Body Profile, Special Assays

Week 12

Completion Outcome Assessment, CRF Clin Exam, Ayu Exam, WHO- Qs & QoL (HR-BHF Qs), AEs

Diagnostic (PCR), Serology (IgM, IgG), Routine haematology Body Profile, Special Assays

***Further Assessment Time Points**: (i) During Hospitalization: Daily monitored vital parameters, disease symptoms, disease progression and recovery, and investigations carried out as per protocol till DISCHARGE; Laboratory and Imaging investigations as per protocol but the study investigator and treating physician can do any additional test as per their judgment (ii)Post DISCHARGE: Daily Telephonic Contact using a special mobile phone application for any relapse or any other symptoms or complications or any other Issue (iii) Discharge: Complete all formalities as required for study completion (iv) Skip week 4 or week 8 end point evaluation within 2 weeks of DISCHARGE

The total study period is 12 weeks; Primary Efficacy is ‘Clinical Recovery’ as described in the protocol; Study participant developing severe COVID 19 or severe complication and requiring special critical support/ ICU/ ventilator support will be withdrawn from the study but followed up to record outcome;

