# 8. STUDY DURATION, FOLLOW- UP SCHEDULE AND PROCEDURES

This is summarized in Figure 1 and Table 1. There are several foot notes provided in Table 1 to further clarify a particular event/test procedure and often with particular reference to the role of the study investigator. Several of the clinical events with reference to clinical examination, study record forms and questionnaires, study procedures, laboratory diagnostics and assessments are elaborated in Appendices enclosed with the protocol (Appendix A to S).

It should be noted that this is a study treatment protocol and that the time to outcome in terms of recovery following onset of illness and/or admission to hospital is a varying parameter. The large majority of study patients are expected to recover completely but based on prior knowledge the mortality of COVID-19 in severe case in well documented (see literature review, section above). It is expected that the majority of patients will recover and be discharged to home within 5 days to 15 days of hospitalization.

However, all study patients who recover are required to follow with the study investigators on pre-determined time points as shown in Table 1.

The total duration of the study is 12 weeks and includes the duration of treatment and post clinical recovery or post-hospital discharge period to ensure optimum recovery and regain of health status.

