# 10. PATIENT POPULATION

The patients will be largely drawn from COVID-19 clinics and outpatients in various medical colleges and hospitals. All patients will be admitted in the hospital for standard care and those willing to participate in the study will be screened and enrolled as described above. Only patients with mild to moderately severe symptoms will be selected as described above. If the patients progress to a severe stage of illness as described below, they will be withdrawn from the study but the investigator will be encouraged to follow the patient ill study completion at week 12 and during this period record the hospital management, course of illness , final outcome and post recovery health status as described in this protocol.

- 1. Inclusion Criteria:

1. Typical Clinical presentation of acute onset febrile illness with cough and a RT_PCR based laboratory confirmation test for COVID-19
2. Patients with either sex, 21to 69years age
3. Patients with Mild to Moderate COVID-19 as described below
4. All patients must agree not to share medication
5. Patients willing to participate and sign an informed consent
   Note: The criteria for mild to moderate COVID-19 are based on the WHO recommendations (See Section 2.5 above with WHO Table on clinical syndromes of COVID-19 and include Mild disease and Uncomplicated Pneumonia but not severe disease which requires any form of intensive care such as invasive techniques for supplemental oxygen or ventilation and life support systems, and absence of any life threatening complications (such as severe respiratory failure, adult respiratory distress syndrome, septicaemia shock and other complications shown in Table 3 above)
   1. Exclusion Criteria

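### A missed daily app entry alerts only the participant's own phone; no written rule tells the site or the central monitoring cell, and it is unclear whether the post-discharge telephone contact is a separate safeguard

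*Combined protocol and SAP*

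**What the plan says.** Section 19.3 has the participant answer the app every evening between 8 and 10 pm, for the whole study. The five cardinal questions are "regarding presence and absence of =Fever, Sore throat, Cough, Breathlessness and Suspected Drug Side Effect"; a sixth asks whether the participant wishes to speak to the investigator. Answers go daily to the local investigator's study computer and to the central monitoring cell (CMC).

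Two alarm rules follow:

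- **Missed entry.** "In case, the study patient fails to complete the response in time", then "the App will raise a frequent alarm bell pop up response on the mobile phone of the study participant". No other recipient is named.
- **YES answer.** "In case, the response is YES to any of the questions", then "there will be an alarm bell type visual and audible response raised both the desktop computer and mobile phone of the local investigator", and the person in charge of the CMC is alerted too. The section gives speedy action by the site as the purpose.

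For the period after discharge, Fig 1 lists "Daily Telephonic Contact using a special mobile phone application for any relapse", other symptoms, complications or other issues. Section 8 expects most participants to be "discharged to home within 5 days to 15 days of hospitalization". Appendix A schedules visits at weeks 4, 8 and 12. Its second note merges the week 4 or week 8 assessments with discharge when discharge falls within two weeks of that time point.

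**The concern.** An entry can be missing because the participant forgot, lost the phone, or became too ill to answer. The rule treats all three alike: the reminder goes to the one person who, in the third case, cannot act on it. The protocol's own account of the disease (the classification part of Section 2) notes that mild cases can occasionally become severe quickly, so the third case is within what the plan foresees.

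Two things are at stake. One is participant safety at home, where the app is the only daily channel the protocol describes. The other is data. Symptom and adverse event information after discharge would be delayed or lost preferentially in participants who deteriorate, in an open-label comparison whose secondary timelines (Section 11.2, up to 28 days) include intensive care admission, ventilation and death. Most participants reach home well inside those 28 days.

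**Working it through.** The plan states no figure on this point, so there is none to reproduce. The check has two parts: reading the rules side by side, and counting days.

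**1. Who learns of a missed entry?**

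| Event | Participant's phone | Local investigator | CMC |
| --- | --- | --- | --- |
| YES to any question (19.3) | not stated | alarm | alarm |
| Entry not completed in time (19.3) | alarm | none stated | none stated |

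Other places that might close the gap:

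- *Daily transmission (19.3).* A gap could be seen at the site or CMC, but nobody is told to look for one or act on it, and no number of missed days is set.
- *Daily telephone contact (Fig 1).* It is described as using a mobile phone application. Section 19.3 says that the app allows two-way contact by SMS and phone call, but not that the site places a call each day.
- *Daily physician assessment (Appendix A footnotes).* No method is given for participants at home, and the table schedules only weeks 4, 8 and 12 after discharge.
- *Personal diary (Section 14).* It is read at monthly visits and at completion.

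None of these turns a missing entry into a site action.

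**2. How long does the exposure last?**

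Inputs: a 12-week study counted from admission (Section 5), which is 12 × 7 = 84 days; a stay of 5 to 15 days for the majority (Section 8); visits at days 28, 56 and 84. Enrolment is assumed to coincide with admission.

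Days at home = 84 − length of stay:

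- stay of 15 days: 84 − 15 = 69 days, 69/84 = 82%
- stay of 5 days: 84 − 5 = 79 days, 79/84 = 94%

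**3. How long until the next scheduled visit?**

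The merge rule applies to week 4 when discharge falls on or after day 28 − 14 = 14.

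| Discharge day | Week 4 merged? | Next visit | Gap after discharge |
| --- | --- | --- | --- |
| 5 | no | day 28 | 28 − 5 = 23 days |
| 14 | yes | day 56 | 56 − 14 = 42 days |
| 15 | yes | day 56 | 56 − 15 = 41 days |

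Participants whose week 4 visit is not merged still face 28-day intervals from week 4 to 8 and from week 8 to 12. These counts take visits on their nominal day; Section 19.10 allows 3 to 5 days either side.

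**The case against.** The strongest reply is that the plan provides other routes. Fig 1 promises daily telephone contact, the app supports calls in both directions, the site and the CMC both receive the daily feed, and participants carry a card with the investigator's details (Section 19.2). Section 19.12 adds that standard operating procedures, not included in the documents, give more detail. A site that did telephone every participant daily would find out about an unanswered call. Clinical recovery, the primary outcome, is judged by a blinded physician under observation and not by the app.

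Part of this stands. The procedures may contain a call-back step, and no direct effect on the primary outcome has been shown. But the card depends on someone using it, the feed has no assigned reader for gaps, and the telephone contact is described as running through an application. If a site-placed call is meant, the protocol does not say so.

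Three stronger readings are tempting and are not supported:

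- *Missed days are counted as symptom-free.* A reader might infer this from the missing alert. The documents give no rule for coding a missed entry; all that can be said is that silence triggers no site action.
- *The site alarm fires every night for every new participant, which buries real signals.* Entry requires "Typical Clinical presentation of acute onset febrile illness with cough and a RT_PCR based laboratory confirmation test for COVID-19", and fever and cough are both alarm questions, so early YES answers are likely. The criterion does not establish that either symptom is present each evening, and Section 10 has all patients admitted, with daily monitoring until discharge. Nor does frequent alarming cause the missing alert, which follows from the missed-entry rule alone.
- *The YES alarm should therefore fire only for a newly reported symptom.* This does not follow. The answers record presence or absence, so such a rule could mute persisting breathlessness, a continuing suspected side effect or a repeated request to speak to the investigator.

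**Conclusion.** The point holds in this form: Section 19.3 directs the alarm for a missed entry to the participant alone, no section escalates non-response to the site or CMC, and the daily telephone contact in Fig 1 is not clearly an independent safeguard. A discharged participant who cannot answer triggers no site alert if the plan is followed as written.

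The exposure is 69 to 79 of 84 days at home (82% to 94%), with a possible 41 to 42 days between discharge and the next scheduled visit for discharge on day 15 or 14. These figures rest on the expected 5 to 15 day stay, enrolment at admission, and visits on their nominal day. They measure time during which the gap matters. They do not estimate how many entries will be missed or how many deteriorations overlooked, for which the documents give no basis. The change is worth making because it is cheap and uses an alert that the plan already has; the finding does not call the primary comparison into question.

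**What to change.** In Section 19.3, extend the alert already sent to the investigator and CMC for a YES answer to any entry still missing when the 8-10 pm slot closes, and have the site log the contact made and its result.

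Reconcile Fig 1 (which appears in both the synopsis and Section 5) with Section 19.3: state whether the daily telephone contact is a call placed by the site or the app questionnaire itself, and who is responsible when no response arrives. If the operating procedures already cover this, a sentence referring to them would do. The rule for YES answers need not change.

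The cost is one app setting and about a paragraph of text. The drawback is some calls to participants who simply forgot.
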